##### Statistical analysis

To examine relationships between perinatal strengths/risk factors and continuous outcomes (eg, Kimberley Mum's Mood Scale (KMMS)), we will use linear or mixed effects regression for repeated measures. Binary outcomes will be analysed using logistic regression, and count outcomes with Poisson or other suitable count models. Analyses will account for the multi-site teletrial design by adjusting for clustering at the site/community level (eg, through random or fixed effects or robust standard errors). For multivariable modelling, candidate predictors will be screened individually, with final model selection guided by Bayesian Information Criteria. Model calibration will be checked graphically, and internal validation performed via bootstrap resampling.

Missing data will be treated case-by-case using multiple imputation when data are plausibly missing at random, and pattern mixture methods with sensitivity analyses when not missing at random mechanisms are likely. Longitudinal mixed-effects models will use all available observations under missing at random assumptions. If differential loss to follow-up occurs, we will apply weighting-based sensitivity analyses (eg, inverse probability of follow-up weighting). Each analysis will include appropriate adjustments for multiple comparisons to balance type I and II error risks.

For the PACT Online and LEAP programmes, effectiveness will be investigated using mixed effects models with programme participation included as the main effect and models adjusted for baseline factors. Differences in characteristics of families who do and do not participate in the programmes will be assessed. If any differences exist, they will be adjusted for in analyses using weighting methods such as propensity matching. Cohort embedded summaries of eligibility, referral and uptake will be reported descriptively. The sensitivity of observational comparisons (eg, uptake vs non-uptake) will be assessed.

An implementation and evaluation analysis will be undertaken and reviewed by the ISC. The RE-AIM framework will be applied to assess the reach, effectiveness, adoption, implementation and maintenance of SFS across all the study sites.^41^ A combination of quantitative metrics (eg, engagement numbers, training outcomes) and qualitative insights from interviews and focus groups will be used. The evaluation will draw on study monitoring data, staff training assessments, participant surveys and yarning interviews to measure how effectively the study is implemented, delivered and taken up. This process ensures comprehensive staff training, strategic resource allocation and identification of site-specific needs while maintaining consistent adherence to the study protocol. Findings for each RE-AIM domain will be summarised using descriptive quantitative indicators and thematic analysis of qualitative data.

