##### Sample size and statistical power

The sample size of 400 families followed prospectively was chosen to provide sufficient power to examine associations between perinatal strengths/risk factors and pregnancy, birth and early childhood outcomes. Assuming approximately 5% of the cohort will have the primary outcome of ‘chance of cerebral palsy/autism spectrum disorder/neurodevelopmental outcome’, this sample gives 80% power (α=0.05) to detect absolute differences of ≥8 percentage points between binary risk factor groups. For more common binary outcomes, differences of >28% can be detected. For continuous outcomes, we will be able to identify between-category differences of >0.3 SD (Z-score units). These estimates are conservative, as repeated measurements over time and mixed-effects models will further improve precision.

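### With about 20 primary events expected, plain logistic regression may give no finite estimate for uncommon exposures; Firth's penalised likelihood would be a cheap safeguard

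*Protocol article*

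**What the plan says.** Under Sample size and statistical power, the protocol article bases its main power statement on a rare event: "Assuming approximately 5% of the cohort will have the primary outcome" (a combined chance of cerebral palsy, autism or another neurodevelopmental outcome). With 400 families, "this sample gives 80% power (α=0.05) to detect absolute differences of ≥8 percentage points between binary risk factor groups".

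Under Statistical analysis, the model for such outcomes is stated in one clause: "Binary outcomes will be analysed using logistic regression". No exception is made for the rare primary outcome. For count outcomes, by contrast, the same sentence leaves room for alternatives to Poisson. Site or community is to be accounted for, for example "through random or fixed effects or robust standard errors". Multivariable models are built by screening predictors one at a time and then selecting by BIC, with bootstrap validation.

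**The concern.** Five per cent of 400 is about 20 events, to be divided between exposed and unexposed families for each strength or risk factor. If a group has no events, the maximum-likelihood log odds ratio is minus or plus infinity. Software then prints a very large coefficient with a meaningless standard error, or drops the term.

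Factors that protect are the most exposed to this, because fewer events among those who have them makes an empty cell more likely. The abstract and the Patient and public involvement section say that the study is to emphasise strengths. An uncommon strength that really does lower risk is therefore the association that the stated method is most likely to leave without a usable estimate. It would then be handled by a decision taken after the data are seen.

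**Working it through.** **Inputs.** From Sample size and statistical power: 400 families, 5% outcome, 80% power, alpha 0.05. From Statistical analysis: logistic regression. Assumed, because the article does not give them: the share of families exposed (5% to 50% shown), a protective risk ratio of 0.5, and the outcome observed in all 400 families. Loss to follow-up would raise the chances below.

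**1. The plan's own figure.** Take 5% as the reference-group rate, 13% in the other group, equal groups and a two-sided test:

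n per group = (A + B)² / 0.08², where A = 1.960·√(2×0.09×0.91) = 0.793 and B = 0.842·√(0.05×0.95 + 0.13×0.87) = 0.337.

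So n = 1.13² ÷ 0.0064 ≈ 200. Two groups of 200 make 400, so the 8 points reproduces.

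**2. Expected events.** 400 × 0.05 = 20. With no association, an exposure held by 10% of families (40) has 40 × 0.05 = 2 expected events.

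**3. Chance of no events among the exposed.** Let s be the share exposed.
- No association: 0.95^(400s).
- Exposure halves risk, overall rate kept at 5%: the exposed risk r solves s·r + (1−s)·2r = 0.05, so r = 0.05/(2−s), and the chance is (1−r)^(400s).

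| Share exposed | Families exposed | No association | Halves risk |
|---|---|---|---|
| 50% | 200 | <0.01% | 0.1% |
| 30% | 120 | 0.2% | 2.8% |
| 20% | 80 | 1.7% | 10.5% |
| 15% | 60 | 4.6% | 19.3% |
| 10% | 40 | 12.9% | 34.4% |
| 5% | 20 | 35.8% | 59.5% |

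For example, at 10% exposure r = 0.05/1.9 = 0.0263, and (1 − 0.0263)^40 = 0.344. Simulation of the exposure estimate itself agrees: no finite estimate in about 12% of runs at 10% exposure with no association, and in about 33% (10% exposure) and 18% (15% exposure) when risk is halved.

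If 5% is instead the rate in the unexposed, the no-association column is unchanged. The halved-risk figures become 0.975^40 = 36% at 10% exposure and 0.975^60 = 22% at 15%.

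**4. What Firth's method does with an empty cell.** Take 0 events in 40 exposed and 20 in 360 unexposed. The maximum-likelihood odds ratio is 0, with log odds ratio minus infinity. For one binary exposure, Firth's estimate equals adding 0.5 to each cell: the odds are 0.5 ÷ 40.5 = 0.01235 in the exposed and 20.5 ÷ 340.5 = 0.06021 in the unexposed, a ratio of about 0.21.

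The fitted risks are then 0.5/41 = 1.22% and 20.5/361 = 5.68%. Their average over the cohort is (40×1.22% + 360×5.68%)/400 = 5.2%, against 5.0% observed. This is why the intercept should be corrected before risks are predicted.

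**5. Site terms.** A site of 40 families has no events with chance 0.95^40 = 12.9%; one of 100 families, 0.95^100 = 0.6%. Entered as a fixed effect, such a site has an infinite coefficient of its own, but it carries no information on the exposure. With nine sites of about 45 families (assumed), 30% exposure and no association, 63% of 5,000 simulated data sets had a site without events, but only 0.1% had an infinite exposure estimate.

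**The case against.** The strongest objection is that a journal article condenses the plan, and that sparse-data estimators and the reported effect measure are commonly left to a fuller document that is not shown. That stands as far as it goes: the silence is not an error, and a full analysis plan may already cover it. What can be commented on is the choice that is printed, a single method for all binary outcomes beside an expected count of about 20 primary events.

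A second objection is that the problem is confined to uncommon exposures, where 20 events are too few to say much in any case. That also stands. Firth's method makes the estimate finite, not informative.

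Three stronger readings are tempting, and the documents do not support them.

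- *That the study's question is a risk difference and the model answers a different one.* The 8 points is a detectable difference in a power statement. The stated aim is to explore associations. Sizing on two proportions and testing by logistic regression is routine and costs little here: at 5% v 13% the log odds ratio is 1.043 and its standard error √(1/10 + 1/190 + 1/26 + 1/174) = 0.387, so a Wald test has power of about 0.77 against 0.80.
- *That results will be reported only as odds ratios.* The article names a model and no effect measure, and a fitted logistic model can be standardised to give risk differences.
- *That an empty site makes the primary association unusable.* Step 5 of the working shows that it normally affects only the site's own coefficient, and the article also allows random effects or robust errors.

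**Conclusion.** The point holds as a low-cost improvement to the stated estimator for the primary outcome. The chance of no finite exposure estimate runs from practically nil for an exposure shared by half the families to about 13% (no association) or 34% (risk halved) for one held by 10%. These figures rest on a 5% overall outcome rate, complete follow-up, and assumed exposure shares and effect. A reader might infer that estimates will fail to exist. The supportable statement is that some may not, depending on how common each exposure turns out to be. Nothing in the article is contradictory on this point, and its 8-point figure reproduces.

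**What to change.** State that the primary outcome, and any other binary outcome with similarly few events, will be fitted by Firth's penalised-likelihood logistic regression with profile-likelihood confidence intervals. Keep logistic regression as written for the more common binary outcomes.

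Say how site enters this model. Firth's method in its standard form has no random site intercept, so one workable choice is to enter the main site regions as fixed categories within the penalised fit, which keeps their coefficients finite too. Say also how the method will be combined with the multiple imputation and BIC selection already planned.

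As a secondary presentation, report the standardised risk difference with its interval from the same model, after correcting the intercept so that the average predicted risk matches the observed rate. That result can then be set beside the 8-point figure.

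The cost is a few sentences and a little more programming, with no new data. The statistical price is slight shrinkage towards no effect. The text should also say that intervals for uncommon exposures will remain wide. With recruitment planned for mid-2026, the change can be made before outcome data exist.

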## Methods and analysis

### Study design and setting

The Strong Families Study (SFS) will be a longitudinal birth cohort study, with nested family support programmes designed to follow 400 Indigenous families in Queensland, Australia, from pregnancy (commencing in mid-2026) through to the child’s fifth year of life. Eligible participants will be assessed at multiple time points from pregnancy through early childhood. Comprehensive measurements and data collection, including biological samples, will be undertaken throughout the study. The measures will encompass a range of health-related themes, gathered from all participating family members.

The study will be conducted as a teletrial model across multiple sites (figure 1), using telehealth technology to enhance equitable access for research participants living in regional, rural or remote areas. The coordinating centre will be based at the Mater Research Institute-The University of Queensland in Brisbane. The study sites include Brisbane (metropolitan), Townsville (regional), Rockhampton (regional) and the Far North Queensland region including Cairns and Mareeba (regionals). In Brisbane, the partnering sites will be the Mater Mothers’ Hospital and Royal Brisbane Women’s Hospital, both quaternary maternity referral hospitals in Queensland. In Townsville, the study has partnered with the Aboriginal Community-Controlled Health Organisation (ACCHO), Townsville Aboriginal and Islander Health Service (TAIHS) and the Townsville University Hospital and Health Service for the protocol design. In Rockhampton, partnerships have been formed with Bidgerdii Community Health Service, Woorabinda Multipurpose Health Service and Central Queensland Hospital and Health Service. In Far North Queensland, the study has partnered with Wuchopperen Health Service, Mulungu Aboriginal Corporation Primary Health Care Service and Cairns and Hinterland Hospital and Health Service. It is likely that some smaller communities from within these regions may also take part once the study commences.

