**Figure 2 F2:**
[figure not shown]
The Strong Families Study recruitment and study visit timeline for participating families. (Note: A detailed description of data collected at each study visit is provided in the online supplemental
table
1).

Following consent, questionnaires will be delivered in person with the help of an Indigenous research assistant or health worker, where possible. A phone option will, however, be made available if requested. In the first two visits, the pregnant participant and, if applicable, their partner complete a series of questionnaires and biological sample collections and undergo initial physical measurements, such as blood pressure and weight. Following birth, the first set of neonatal data is collected, including body measurements and a chart review conducted by a midwife. Subsequent in-person visits will occur throughout the study period, except between 12 and 16 weeks postpartum during which parents are asked to record a 3-min video of their baby’s spontaneous movements for neurodevelopmental assessment (on the General Movements Assessment) (figure 2).^36 37^ Child neurodevelopmental assessments will continue to occur at each visit postbirth. Infants with a confirmed or high chance of a neurodevelopmental disability will be referred to the appropriate family support programmes available within the SFS.^27^,^29^

At the request of the ISC, all study surveys and instruments will be delivered in-person as the first preference using a yarning method, which encourages more informal and relaxed discussions between researchers and participants.^38^,^40^ Furthermore, a health education component will be embedded into the yarns following data collection to increase health literacy and promote healthy behaviours to grow health knowledge in participants of the study. To ensure all team members are appropriately trained and consistent in their approach, yarning guides co-designed by the ISC will be embedded within the electronic data collection forms used for the surveys.

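### Robust standard errors are listed as an acceptable adjustment for site clustering, but with 4 to 5 sites they are too small unless a few-cluster correction is used

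*Protocol article*

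**What the plan says.** The Statistical analysis section of the protocol article commits the analyses to "adjusting for clustering at the site/community level (eg, through random or fixed effects or robust standard errors". The list is open, ranks none of the three methods and names no small-sample correction.

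On the number of clusters, Study design and setting states: "The study sites include Brisbane (metropolitan), Townsville (regional), Rockhampton (regional) and the Far North Queensland region including Cairns and Mareeba (regionals". That is four regions, or five places if Cairns and Mareeba are split. The same section names ten partner hospitals and services: two in Brisbane, two in Townsville, three in Rockhampton and three in Far North Queensland. It adds: "It is likely that some smaller communities from within these regions may also take part once the study commences".

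On the unit of observation, measures are "gathered from all participating family members", and under Study regimen "the pregnant participant and, if applicable, their partner complete a series of questionnaires and biological sample collections". No family-level term is named. The sample is counted in families: "The sample size of 400 families followed prospectively".

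**The concern.** The cluster-robust variance estimate relies on a large number of clusters, not of families. With four or five clusters it is built from four or five score totals. It is then biased downward and very noisy, and a 1.96 cut-off ignores both defects. Confidence intervals come out too narrow and p-values too small.

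The three listed methods are therefore not equivalent at this number of sites: one holds its nominal error rate and another, in its plain form, does not. The study will test many exposures against many outcomes, so an inflated error rate per test would produce spurious strengths and risk factors in findings meant to inform policy and services.

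**Working it through.** **The plan's own figure.** The article gives no figure for clustering. Its only related figure is "this sample gives 80% power (α=0.05) to detect absolute differences of ≥8 percentage points between binary risk factor groups". Taking 5% versus 13%, equal groups and a two-sided test (sidedness is not stated):

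n per group = [1.96·√(2·0.09·0.91) + 0.8416·√(0.05·0.95 + 0.13·0.87)]² / 0.08² = (0.793 + 0.337)² / 0.0064 ≈ 200, so 400 in total, with power 0.801.

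The figure reproduces and contains no allowance for clustering. It is context only; the point here concerns the analysis method.

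**Inputs for the clustering check.**
- From the article: N = 400; clusters G = 4 or 5 (sites) or 10 (named services); robust standard errors permitted; no correction named.
- Assumed, because not given: site ICC 0.01 to 0.05; a binary exposure with prevalence about 40% that varies moderately between sites; equal site sizes unless stated; linear outcome; no true effect.

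**Methods compared**, 2,500 runs per setting (Monte Carlo error at 5% is √(0.05·0.95/2500) ≈ 0.4 points):
- Uncorrected robust SE, 1.96 cut-off.
- CR1: robust SE × √[G/(G−1) · (n−1)/(n−2)], 1.96 cut-off.
- CR1 with a t(G−1) cut-off.
- Site fixed effects with the ordinary model-based SE.

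**Type I error at nominal 5%** (ICC 0.01 / 0.05):

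| Clusters | Uncorrected, z | CR1, z | CR1, t(G−1) | Site fixed effects |
|---|---|---|---|---|
| 4 | 19.7 / 21.0% | 15.1 / 16.6% | 5.2 / 5.2% | 6.2 / 5.3% |
| 5 | 16.7 / 16.9% | 12.9 / 13.2% | 5.4 / 5.2% | 5.4 / 4.9% |
| 10 | 10.1 / 10.2% | 8.9 / 8.5% | 5.6 / 5.2% | 5.7 / 4.9% |
| 20 | 7.6 / 6.9% | 6.9 / 6.3% | 5.4 / 4.5% | 5.5 / 4.8% |
| 40 | 5.0 / 6.3% | 4.8 / 5.9% | 4.2 / 4.8% | 4.9 / 5.0% |

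A repeat simulation under the same ICC range gave 15–20% with 4 clusters, 12–16% with 5 and 8–10% with 10 for the z-tests. Together: about 12–21% with 4 or 5 clusters, and 8–10% with 10.

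**Why.** The uncorrected robust SE averages 0.73–0.77 of the true standard deviation with 4 sites and 0.79–0.82 with 5. Shrinkage to 0.75 alone gives P(|Z| > 1.96·0.75) = P(|Z| > 1.47) ≈ 14%. The rest comes from noise in the SE itself.

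**Variations.**
- Four uneven sites (200, 80, 60, 60; ICC 0.02): uncorrected 21.3%, CR1 with z 16.0%, CR1 with t 6.3%, fixed effects 4.7%.
- Binary outcome at 5%, logistic regression, site SD 0.3 on the logit scale, exposure about 30%: robust z-test about 14%, 11% and 8% with 4, 5 and 10 clusters; fixed effects 3–5%.
- Exposure that varies only between sites (ICC 0.02): CR1 with t(G−1) still gives 12.7% with 4 sites and 10.0% with 5. Fixed effects cannot estimate such an effect.

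**Level of the fixed effect.** A 5% outcome gives 400·0.05 = 20 events. With equal clusters that is 5 per site for four sites but 2 per service for ten. Using a Poisson approximation, the chance that at least one cluster has no event is 1 − (1 − e⁻⁵)⁴ ≈ 3% for four sites and 1 − (1 − e⁻²)¹⁰ ≈ 77% for ten services. For the rare outcome, fixed effects are workable by site but not by service.

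**Families (secondary).** If two parents' outcomes are pooled on an exposure shared by the family, the variance is multiplied by 1 + ρ. For assumed ρ = 0.1 to 0.4, ignoring this makes SEs 5% to 16% too small (type I error 6.2% to 9.8%). For a mother-versus-partner contrast the factor is 1 − ρ, so the naive SE is too large (type I error 3.9% down to 1.1%).

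**The case against.** The strongest reply is that the article fixes nothing here. Its list is introduced as examples, it includes the sound option, and the choice of method, correction and reference distribution is ordinary analysis-plan detail. That stands in part. A reader might infer that the study's false-positive rate will be about three times nominal; the text does not support this. The inflation belongs to one option in its uncorrected form, and an analysis plan not shown may exclude or correct it. What remains is that a published list offers, without qualification, a method whose plain form is unsound at the article's own number of sites.

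A second reply is that the clustering level is site or community, so there may be more than 4 or 5 clusters. That is fair, and the number is not stated. But ten clusters still give 8–10%, and the error approaches nominal only at about 20 to 40.

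A reader might also infer that the absence of a family term makes error bars too small across the study, because both parents are measured. The documents do not support that. The stated aims concern maternal, neonatal and child outcomes, normally one record per family (multiple births aside), and the example outcome, the KMMS, is a mother's scale. Nowhere does the article say that both parents' outcomes will be pooled. Where they were, the direction of the bias depends on the contrast. Site-level robust errors would also absorb within-family correlation, since families nest within sites.

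**Conclusion.** The point holds in a limited form. Site-level robust standard errors, used with a normal cut-off and no few-cluster correction, are not a safe choice for this study. Their SEs are on average about 18–27% too small with 4 or 5 sites before any correction. Site fixed effects, or CR1 with t(G−1), hold about 5% for exposures that vary within site.

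These sizes rest on an assumed site ICC of 0.01 to 0.05, an assumed spread of exposure between sites, and mostly a linear outcome; the logistic check at 5% prevalence points the same way. The random-effects option was not simulated and no claim is made about it. The family term is a clarification for pooled models only and does not affect the main aims.

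**What to change.** In the Statistical analysis section or the analysis plan:

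1. Name site (4 or 5 levels) as a fixed effect by default in models for exposures that vary within site.
2. Allow site-level robust standard errors only as a sensitivity analysis and only with a few-cluster correction, for example CR1 with a t(G−1) reference or a wild cluster bootstrap.
3. Define what counts as a cluster: region, service or community.
4. Report purely site-level factors such as remoteness descriptively.
5. Secondary: add a family random intercept to any model that pools both parents' outcomes or siblings.

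The cost is a few sentences and 3 to 4 degrees of freedom. The real loss is that site-level effects cannot be estimated in the fixed-effects models. With 4 or 5 sites even the corrected robust test gave 10–13% error for such effects, so little dependable inference is given up.

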Co-design underscores the importance of collaborating with key stakeholders through capability building, sharing decision-making, and the development of equitable, sustained partnerships.^16 17^ Co-design values consumer-driven research and engagement throughout all stages of the research process, using Aboriginal Participatory Action Research to ensure Indigenous voices are central and the study remains relevant and aligns with community priorities and needs.^17^,^20^ The integration of an Indigenous lens within these processes facilitates the recognition and integration of Indigenous knowledge systems and the opportunity for cultural considerations that have historically been overlooked in previous policies and mainstream research.^21^ Furthermore, such approaches can counter the pervasive deficit discourse research relating to Indigenous health and well-being, which are often negative and disempowering.^22 23^ By using Indigenous voices and lived experiences, co-design highlights the strengths and resilience of Indigenous peoples, framing these as essential pathways to self-determination and sovereignty rights.^24 25^ This co-design approach ensures the development and application of culturally sensitive methodologies that are more likely to be valued by the community they aim to serve.^18^ Overall, a co-design process underpins ethical reciprocal research, emphasising empowerment and equity to ensure meaningful, sustainable and beneficial outcomes for the community.

This paper describes the research protocol and methodology for The Strong Families Study, a co-designed, Indigenous-led, prospective longitudinal study of Indigenous families in Queensland, Australia. This birth cohort study aims to examine the perinatal strengths and risk factors among reproductive-aged Indigenous parents. Specifically, it seeks to explore associations between these parental strengths and potential risk factors and (1) maternal pregnancy outcomes, (2) neonatal and birth outcomes and (3) early childhood developmental outcomes, with the overarching goal of informing evidence-based policy and practice change. Families will be followed at multiple time points, throughout pregnancy and early childhood.

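### Covariates for the association models are chosen by one-at-a-time screening and BIC, which with about 20 to 36 primary events usually drops moderate confounders and can leave exposure estimates confounded

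*Protocol article*

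**What the plan says.** The Introduction states an association aim: "it seeks to explore associations between these parental strengths and potential risk factors" and pregnancy, birth and child outcomes. *Sample size and statistical power* repeats it: "The sample size of 400 families followed prospectively was chosen to provide sufficient power to examine associations".

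In *Statistical analysis*, "Binary outcomes will be analysed using logistic regression". For multivariable models, "candidate predictors will be screened individually, with final model selection guided by Bayesian Information Criteria". The next sentence adds: "Model calibration will be checked graphically, and internal validation performed via bootstrap resampling".

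No confounder is named as retained whatever the selection shows. Site or community clustering is handled separately. Only the PACT Online and LEAP comparisons are said to be adjusted for baseline factors, with weighting where participants and non-participants differ.

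On the primary outcome, the article writes "Assuming approximately 5% of the cohort will have the primary outcome" and that "this sample gives 80% power (α=0.05) to detect absolute differences of ≥8 percentage points between binary risk factor groups".

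**The concern.** Screening, BIC, calibration and bootstrap validation are the steps for building a prediction model. An association question needs something else: the variables that confound the exposure should be in the model whether or not they reach a statistical threshold in this sample.

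With a rare outcome, a real confounder often fails such a threshold. Once it is dropped, its effect is partly credited to the exposure. The final model's standard error also treats the selected model as if it had been fixed in advance.

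The study is meant to inform policy and practice, so a null exposure reported as a risk or a strength could mislead partner services and communities.

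**Working it through.** **Inputs from the article:** 400 families; primary outcome about 5%; 80% power at α=0.05 for a difference of 8 percentage points; logistic regression; screening, then BIC. **Not given, so assumed:** two-sided α and equal groups for the power check; screening cut-off; number of candidates; confounder strengths; exposure prevalence.

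**1. The stated power and the event count.** For 5% versus 13% in equal groups, mean 9%:

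n per group = [1.96·√(2·0.09·0.91) + 0.842·√(0.05·0.95 + 0.13·0.87)]² / 0.08² = (0.793 + 0.337)² / 0.0064 ≈ 200.

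So 400 families give power 0.801, and the stated figure reproduces. This case implies 200·0.05 + 200·0.13 = 36 events. Reading 5% as the whole-cohort rate gives 400·0.05 = 20 events, but then 1% versus 9% has power 0.959, not 0.80. Both counts are carried forward, before any loss to follow-up.

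**2. The BIC threshold.** One extra parameter must raise the likelihood-ratio χ² by more than ln(400) = 5.99, that is |z| > 2.448, p = 0.0144.

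**3. Chance that a moderate confounder passes.** For OR 1.5 per SD and a 5% outcome, the expected z ≈ ln(1.5)·√(400·0.05·0.95) = 0.405·4.36 = 1.77. P(|Z + 1.77| > 2.448) ≈ 0.25, before the screening step.

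**4. Effect on the exposure estimate.** Simulation assumptions: n=400, about 20 events, 20 candidates of which three are confounders (OR 1.5 per SD with the outcome, all in the same direction), screen at p<0.10, exposure forced in, true exposure OR 1. The two values in each cell come from two separate runs, of 400 and 600 data sets per setting.

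| Confounder–exposure OR per SD | Median exposure OR | Type I error |
|---|---|---|
| 1.2 | 1.17, 1.17 | 7%, 4% |
| 1.5 | 1.28, 1.28 | 7.5%, 10% |
| 2.0 | 1.65, 1.54 | 18%, 17% |
| 2.5 | 1.83, 1.78 | 26%, 26% |

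A third run gave 1.15 and 7% at the weak end and 1.83 and 27% at the strong end. Across the runs each confounder was kept 15–23% of the time. With about 36 events and confounder–exposure OR 2.0, confounders were kept 34% of the time, the median OR was 1.50 and type I error 25%. More events at this scale do not remove the problem.

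Forcing in the three confounders by ordinary logistic regression gave median OR 0.93–1.03 and type I error 2–5.5%.

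**5. A second design, to see where the harm is small.** Binary confounders (prevalence 30%), exposure prevalence 40%, screen at p<0.05, about 20 events, true OR 1.

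| Confounders | OR with outcome | OR with exposure | Each kept | Median OR, selected | Coverage, selected | Coverage, all forced in |
|---|---|---|---|---|---|---|
| 4 | 1.5 | 2.5 | 4% | 1.26 | 0.927 | 0.961 |
| 4 | 2 | 2.5 | 14% | 1.47 | 0.861 | 0.958 |
| 4 | 3 | 2.5 | 37% | 1.42 | 0.853 | 0.956 |
| 4 | 1.5 | 1.5 | 6% | 1.11 | 0.942 | 0.949 |
| 4 | 2 | 1.5 | 15% | 1.14 | 0.942 | 0.965 |
| 1 | 2 | 2.5 | 16% | 1.08 | 0.952 | 0.966 |

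**6. Interval width.** In the first three rows, mean model SE against empirical SD is 0.49 v 0.50, 0.49 v 0.56 and 0.51 v 0.60. The shortfall therefore runs from 2% (0.49/0.50) to 15% (0.51/0.60). Most of the lost coverage comes from bias.

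**The case against.** The strongest reply is that this is a condensed article. Selection is only guided by BIC, the text speaks of candidate predictors and not of adjustment sets, the aim is exploratory, and a fuller plan might list confounders that are always kept. That would count if the article were silent. It is not: it states a selection method and gives no other covariate rule for the association models.

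Nor do the named safeguards help. Calibration and bootstrap validation assess prediction and cannot restore a dropped confounder, and the text does not say that selection is repeated in each resample. Multiplicity adjustment does not remove confounding.

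The reply is right that the harm is conditional. Four stronger readings that a reader might infer are not supported:

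- *Primary associations will be biased and falsely significant.* The article gives no confounder strengths. Large bias needs several confounders acting in the same direction, each strongly tied to the exposure.
- *Twenty events allow only about two adjustment terms.* Four forced confounders plus the exposure (20/5 = 4 events per parameter) still gave coverage of 0.949–0.965.
- *The surviving model is largely chance.* In the 20-candidate simulation a noise variable survived in 21–27% of runs, so roughly three-quarters of final models contained none.
- *All outcomes are equally affected.* Every figure here concerns the rare primary outcome.

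**Conclusion.** The point holds and should be fixed. It is a mismatch between a stated method and a stated aim. For the primary outcome, with 20 to 36 events, confounders of OR 1.5 per SD are retained only about 15–40% of the time, so exposure estimates can carry residual confounding. Intervals that ignore the selection are a lesser problem.

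Under the assumptions of step 4 and about 20 events, the median OR for a null exposure lies between about 1.15 (type I error 4–7%) and about 1.8 (26–27%). Where in that range the study would fall cannot be told from the article. With a single confounder or weak ones, the median OR was 1.08–1.14 and coverage 0.942–0.952, close to nominal. Continuous and common outcomes carry more information and should be less exposed, but this was not computed.

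**What to change.** In *Statistical analysis*, replace screening and BIC for the association aims. For each exposure–outcome question, choose a small confounder set beforehand on subject knowledge (a causal diagram is a convenient way to record it), and keep it in the model regardless of p-value or BIC. For the rare primary outcome, Firth-penalised logistic regression is an optional safeguard; ordinary logistic regression behaved acceptably with three or four forced confounders.

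Confine screening, BIC, calibration plots and bootstrap validation to models declared as predictive, and state that screening and selection are repeated inside every bootstrap sample.

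The cost is a change of wording, some planning work with subject experts and slightly wider intervals. In the first three rows of step 5, mean model SE rose from 0.49, 0.49 and 0.51 to 0.53, 0.54 and 0.55 when all four confounders were forced in, an increase of about 8–10% (0.53/0.49 = 1.08; 0.54/0.49 = 1.10; 0.55/0.51 = 1.08). No change to recruitment or data collection follows, provided the chosen confounders are among the variables already collected.
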